## 6. Statistical Considerations

### 6.1 Analysis Sets

#### *6.1.1 Safety Analysis Set*

The safety analysis set will consist of all subjects with whom the study treatment was initiated.

#### *6.1.2 Primary Efficacy Analysis Set*

The primary endpoint parameter: *improvement in fibromyalgia questionnaires scores* will be measured following the 1st treatment period and separately after the crossed treatment period.

The primary efficacy analysis evaluation will include all subjects who completed the treatment period, had no major protocol violations.

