## 4. Study endpoints

### 4.1 Primary endpoint

The primary end point of the study will be the measurement of daily pain on a (0-10) Visual analogue Scale (VAS) [42]

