### 4.2 Secondary endpoint

The secondary end-points of the study will include the following:

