#### *4.2.1 Fibromyalgia syndrome symptoms and quality of life questioners*

- Global Pain Scale (GPS) [43].
- Patient global impression of change (PGIC) [44]
- Fibromyalgia Impact Questionnaire (FIQ, Hebrew version) [45]
- Wide Spread Pain Index (WPI) and Symptom Severity Scale (SSS) [46]
- Quality of Life (SF-36) [47]
- Medical Outcome Sleep Scale (MOS) [48]
- Beck Depression Inventory (BDI-II) [49]
- Quality of life will be evaluated by the EQ-5D
- The Brief Symptom Inventory-18 (BSI-18) [50]

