##### **6.1.2.1 Sample Size Considerations**

According to Initiative on Methods, Measurement, and Pain Assessment in Clinical Trials (IMMPACT) recommendations, pain intensity reductions of 30% to 50% or more are considered useful. Therefore, the estimated sample size was calculated based on a reduction of 50% in the HBOT group and a reduction of 20% in the medication group, with a standard deviation of 40% [65, 66]. Assuming a power of 80%, and 5% two-sided level of significance, a total of 58 participants would be required, 29 participants in each arm. Considering a dropout rate of 15% the total sample size required is 70.

|                                                     |                                                        |                                        |
|-----------------------------------------------------|--------------------------------------------------------|----------------------------------------|
| Investigational Product
Hyperbaric chamber       | Short Title:                                           | Protocol No.
058-17-ASF             |
| Phase:
Investigator Initiated Phase
III study | Hyperbaric Oxygen Therapy for Fibromyalgia
Syndrome | Version, Date
Ver.4.0, 10 OCT, 2017 |

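### Sections 4.1 and 6.1.2 name different primary endpoints, and the stated 80% power has a basis only for the pain endpoint

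*Protocol*

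**What the plan says.** Four places in the protocol bear on the primary endpoint.

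- **Section 4.1** names a single measure: "The primary end point of the study will be the measurement of daily pain on a (0-10) Visual analogue Scale (VAS"). It gives no time point and no change metric.
- **Sections 4.2 and 4.2.1** put the symptom and quality-of-life questionnaires under a different label: "The secondary end-points of the study will include the following". There are nine entries (GPS, PGIC, FIQ, WPI/SSS, SF-36, MOS, BDI-II, EQ-5D, BSI-18), or ten if WPI and SSS are counted apart. One of them is "Fibromyalgia Impact Questionnaire (FIQ, Hebrew version"). The pain VAS is not in this list.
- **Section 6.1.2** describes the primary endpoint parameter as "improvement in fibromyalgia questionnaires scores", taken after the first "treatment period and separately after the crossed treatment period". No instrument is named.
- **Section 6.1.2.1** starts from the benchmark that "pain intensity reductions of 30% to 50% or more are considered useful" and sizes the trial on "a reduction of 50% in the HBOT group and a reduction of 20% in the medication group", with a standard deviation of 40%.

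Section 3.2.3 supplies the only relevant timing: after 3 months, once the 2nd evaluation is done, patients in both arms are offered the other treatment.

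**The concern.** A protocol should give one answer to the question of which outcome decides the trial, and this one gives two. By section 4.1 the deciding outcome is a single pain scale. By section 6.1.2 it is an unspecified group of questionnaire scores that section 4.2 has already classed as secondary. Both statements stand in the current Version 4.0 text, and nothing in the document ranks one above the other.

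Two things are at stake. An analyst working from section 6 could test a different outcome from the one in section 4 and still claim to follow the protocol. And the power statement was derived for pain intensity, so it says nothing about a questionnaire. This matters more in a study labelled Phase III whose objectives section says HBOT must show a clear advantage over standard care to justify its burden.

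**Working it through.** **1. Reproduce the stated sample size.** Inputs from section 6.1.2.1: reductions of 50% and 20%, so a difference of 30 percentage points; SD 40; two-sided alpha 0.05; power 80%; dropout 15%. Section 5.4 gives 1:1 allocation.

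- Standardised effect: 30/40 = 0.75.
- Normal approximation: n per arm = 2 × (1.960 + 0.842)² × (40/30)² ≈ 27.9, so 28.
- Two-sample t-test: 28.9, so 29 per arm and 58 in total. Power at 29 per arm is 80.1%.
- Dropout: 29/0.85 = 34.1, so 35 per arm and 70 in total.

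The plan's 29, 58 and 70 are all recovered. The 80% therefore describes one comparison of percent pain reduction at an unsplit 5%.

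**2. Ask what that power covers.** Section 6.1.2.1 refers to pain intensity and does not name the VAS. Linking it to section 4.1 is an inference, but a natural one, because 4.1 is the only pain-intensity measure designated primary. The protocol gives no effect size or SD for any questionnaire, so power for the 6.1.2 endpoint cannot be computed from it. For illustration only, with assumed standardised effects that are not in the protocol, 29 per arm gives:

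| Assumed effect | Power at two-sided 5% |
|---|---|
| 0.5 | 46.5% |
| 0.6 | 61.2% |
| 0.75 | 80.1% |

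**3. Size the multiplicity if 6.1.2 were read as several tests.** Section 6.1.2 does not say how many questionnaires it means, so the number k is an assumption and a range is needed. By name, only FIQ and WPI/SSS are clearly fibromyalgia-specific, which gives k = 2, or 3 with WPI and SSS apart. The widest reading is the whole 4.2.1 list, k = 9 or 10. With each score tested at 5% and independence assumed, the family-wise error is 1 − 0.95^k:

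| k | Family-wise error |
|---|---|
| 2 | 1 − 0.9025 = 9.8% |
| 3 | 1 − 0.8574 = 14.3% |
| 9 | 1 − 0.6302 = 37.0% |
| 10 | 1 − 0.5987 = 40.1% |

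These scales are completed by the same patients about overlapping symptoms, so positive correlation is to be expected. It moves each figure down towards 5%, which would be reached only if the scores were perfectly correlated.

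**The case against.** The strongest reply is that the intent is clear enough. The heading of section 4.1, the secondary label in section 4.2 and the basis of the sample size all point to pain. The conflicting phrase is one sentence under a heading about analysis sets. This stands as evidence of which endpoint was probably meant, and it is why the fix goes in that direction. It does not remove the contradiction, because section 6.1.2 explicitly uses the term primary endpoint. Nor does it help to read the phrase loosely as including the VAS: the wording is plural and would make the VAS one of several primary scores.

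A second reply is that the statistical analysis plan, which is not shown, may settle the matter. Multiplicity rules can properly be left there. The identity of the primary endpoint, once the protocol has stated it in two incompatible ways, cannot.

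Three stronger readings are tempting, and the document does not support them.

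- **Success may be claimed on pain or on any of nine or ten questionnaires.** No such rule is stated. Section 6.1.2 names no instrument, so nine or ten tests is only the widest reading.
- **The two measurement times double the number of tests.** Eighteen or twenty independent tests would give 60.3% or 64.2%. That treats repeat readings of the same scale in the same patients as independent. It also treats the post-crossover reading as a second confirmatory test, whereas section 6.1.2 says only that the parameter is measured then, separately.
- **The sample size is wrong.** It is not; it reproduces for the variable it uses.

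**Conclusion.** The contradiction is real and is wrong as written: sections 4.1 and 6.1.2 designate different outcomes as primary, and no current text reconciles them. The 80% power is correct for one comparison of percent pain reduction. It has no basis for any questionnaire if 6.1.2 governs.

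The possible error inflation is conditional. It arises only if several questionnaires were each tested at 5% without adjustment. It is then about 10-14% for two or three fibromyalgia-specific scores and 37-40% for the full list. Both ranges assume independence and are upper illustrations, given the positive correlation expected. They are not error rates that the protocol commits to. The case for correction rests on the conflicting statements and does not depend on which figure applies.

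**What to change.** In section 6.1.2, replace the questionnaire wording with the section 4.1 endpoint, and state it identically in both sections: percent change from baseline in daily pain VAS at the 2nd evaluation (3 months, end of the first treatment period, before the switch is offered), compared between randomised arms. The measure comes from 4.1, the time point from 3.2.3 and the percent metric from 6.1.2.1. Section 4.1 alone supplies neither of the last two. Name the VAS in the sample-size paragraph so that the link is explicit.

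Also state in 6.1.2 that the 4.2.1 questionnaires and all post-crossover measurements are secondary, so that the second reading keeps a defined role.

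The cost is a short protocol amendment. The sample size stays at 29 evaluable per arm and 70 in total, and no visit changes. The sponsor gives up a primary claim on a questionnaire. If it prefers a questionnaire endpoint, it would have to name the instrument or instruments, set a multiplicity rule if there is more than one, and justify the power afresh.

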## 1.2 HBOT

HBOT is a well-known and reliable therapeutic modality, which has been implemented in a variety of clinical conditions. HBOT, the application of hyperbaric pressure in conjunction with increased oxygen content, has been shown in several clinical studies to have the capacity to induce neuroplasticity in injured brains even years after an acute insult [11-17]. HBOT induces neuroplasticity by stimulating cell proliferation [18], promotes neurogenesis of endogenous neural stem cells [19], regenerates axonal white matter [20], improves maturation and myelination of injured peripheral and cranial neural fibers [21, 22], induces brain angiogenesis[12], and stimulates axonal growth thus increasing the ability of neurons [23, 24]. To date, two prospective randomized controlled trials have demonstrated the efficacy of HBOT in fibromyalgia [25, 26]. The improvement was demonstrated in all aspects of FMS including pain threshold, fatigue, distress and quality of life [25, 26].

A growing amount of evidence has been accumulating over recent years regarding the efficacy of HBOT in the treatment of PPCS such as those caused by mTBI[27], which is defined as alteration of brain function caused by external forces, with one or more of the following: loss of consciousness for a duration of 0–30 minutes, posttraumatic amnesia for a duration of less than 24 hours, and Glasgow Coma Scale grade of 13–15 [28]. Specifically, HBOT appears to be capable of inducing cerebral angiogenesis, thus improving perfusion to chronically damaged brain tissue even months to years after the injury [29]. Thus, as recently reviewed by Figueroa et al, 5 out of 5 peer-reviewed clinical trials have demonstrated therapeutic effects of HBOT on symptoms of mTBI/PPCS as well as PTSD [30].

One possible mechanism explaining the neuro-plasticity potential of HBOT relates to the effect on the mitochondrial function of Glia cells [31], a cell population which is postulated to play an integral role in the pathogenesis of central sensitization and chronic pain [32, 33]. Breathing oxygen under hyperbaric conditions has the capacity to significantly increase brain oxygen tension, increasing tissue oxygenation and oxygen delivery into Glial mitochondria [34, 35].

|                                                     |                                                        |                                        |

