### 3.2.3 Crossover

After 3 months of either pharmaceutical or HBOT, once the 2nd evaluation is completed, all patients in both groups will be offered to switch to the alternative treatment group.

|                                                     |                                                        |                                        |
|-----------------------------------------------------|--------------------------------------------------------|----------------------------------------|
| Investigational Product
Hyperbaric chamber       | Short Title:                                           | Protocol No.
058-17-ASF             |
| Phase:
Investigator Initiated Phase
III study | Hyperbaric Oxygen Therapy for Fibromyalgia
Syndrome | Version, Date
Ver.4.0, 10 OCT, 2017 |

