### 5.4 Randomization and handling of the control group

Since the diversity of the patients included in the study, after signing the informed consent is expected to be high, no stratifies criteria will be used. Patients will be randomized in 1:1 fashion to either HBOT or pharmaceutical group.

|                                                     |                                                        |                                        |
|-----------------------------------------------------|--------------------------------------------------------|----------------------------------------|
| Investigational Product
Hyperbaric chamber       | Short Title:                                           | Protocol No.
058-17-ASF             |
| Phase:
Investigator Initiated Phase
III study | Hyperbaric Oxygen Therapy for Fibromyalgia
Syndrome | Version, Date
Ver.4.0, 10 OCT, 2017 |

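### Section 6.1.2 gives primary status to a reading taken after an optional switch, which cannot estimate the HBOT-versus-medication effect without bias, and does not say which of its two readings decides

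*Protocol*

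**What the plan says.** Protocol section 6.1.2 has the primary endpoint parameter measured after the first "treatment period and separately after the crossed treatment period". It ranks neither reading. The same section limits the primary efficacy set to subjects who finished treatment without a major violation, and does not say which period's treatment is meant.

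Section 5.4 randomises once, to the starting treatment: "Patients will be randomized in 1:1 fashion to either HBOT or pharmaceutical group". Section 3.2.3 then says that after 3 months, when the 2nd evaluation is done, "all patients in both groups will be offered to switch to the alternative treatment group". No interval between the periods is stated. The only drug-free interval in the protocol is the two weeks before recruitment in section 3.1.

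Section 6.1.2.1 sizes one contrast, "a reduction of 50% in the HBOT group and a reduction of 20% in the medication group", with a standard deviation of 40%, 80% power and one "5% two-sided level of significance". It arrives at 29 per arm, 58 evaluable, and 70 after allowing for 15% dropout.

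Section 4.1 and section 6.1.2 name the primary endpoint differently. That is a separate matter and is not part of this point.

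**The concern.** The first-period reading compares two randomised groups before anyone has switched. The second reading differs in four ways.

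- **Selection.** The starting treatment is randomised, but acceptance of the switch is the patient's choice, made after living through the first treatment. The analysis set then removes those who do not complete.
- **No return to the starting state.** The offer comes directly after the 2nd evaluation, with no stated washout.
- **A different population.** Section 3.1 excludes anyone previously given HBOT, or currently or previously given duloxetine or pregabalin. After period 1, HBOT-first patients have had HBOT, and medication-first patients have been offered one of those two drugs (section 3.2.2). Period 2 is therefore largely made up of patients with exposures that would have barred them from period 1.
- **Carry-over.** Section 1.2 attributes the HBOT effect to structural processes such as new vessels, axonal growth and myelination. It is plausible that these do not reverse at once, although the protocol gives no duration of benefit.

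Once patients have had both treatments, a comparison between arms at the end of period 2 compares orders of treatment. A before-and-after change within switchers mixes treatment with carry-over, time trend, regression to the mean and selective switching. A favourable or unfavourable crossed-period result could then be presented as a primary finding with equal textual support.

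**Working it through.** **1. Reproducing the plan's sample size.** Inputs from section 6.1.2.1: difference 50 − 20 = 30 points, SD 40, two-sided alpha 0.05, power 0.80.

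- Normal approximation: n per arm = 2 × [40 × (1.960 + 0.842) / 30]² = 27.9, rounded up to 28.
- Two-sample t-test, standardised effect 30/40 = 0.75: 28.9, rounded up to 29 per arm, or 58 in total. Power with 29 per arm is 80.1%.
- Dropout: 29 / 0.85 = 34.1, rounded up to 35 per arm, or 70 in total.

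The stated 58 and 70 are exactly what one two-arm comparison at one 5% level needs. That contrast exists only in period 1, and nothing in the figure allows for a second primary reading.

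**2. What the second reading would show.** Assume that everyone switches, that medication-first patients reach the planned 50% reduction from the original baseline after HBOT, and that a share p of the 50% HBOT effect persists in HBOT-first patients. Take their end-of-period-2 reduction as the larger of 20% (medication) and p × 50% (what persists). The difference between sequences is then 50 − max(20, 50p).

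| Assumed p | HBOT then medication | Medication then HBOT | Difference |
|---|---|---|---|
| 0% | 20 | 50 | 30 |
| 50% | 25 | 50 | 25 |
| 75% | 37.5 | 50 | 12.5 |
| 100% | 50 | 50 | 0 |

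The assumed true effect is 30 points in every row. Under this simple rule the reading recovers it only while the persisting part stays below the medication effect (50p ≤ 20, so p ≤ 40%), and only with full switching. The persistence share and the larger-of-two rule are assumptions. The documents give neither.

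**3. Error rate if either reading could count.** With two tests at 5% two-sided, independent: 1 − 0.95² = 9.75%. With correlated normal test statistics: 1 − P(|Z₁| < 1.96 and |Z₂| < 1.96), which gives 9.5%, 9.1% and 7.0% at assumed correlations of 0.3, 0.5 and 0.9.

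**4. Price of keeping two primary readings.** Splitting alpha to 0.025 each needs 36 per arm by t-test, so 72 evaluable and 72 / 0.85 = 84.7, or 85 enrolled. With the planned 29 per arm, power at 0.025 is 70.9%. Splitting alpha would not remove the bias shown in step 2.

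**The case against.** The strongest reply is that the protocol already points to period 1. The sample size fits that contrast alone, and the 3-month data are collected before any switch, so the crossed period cannot contaminate them. Section 6.1.2 says the parameter is measured, not tested, at the two times, and an SAP that is not shown may set a hierarchy. All of this is fair. It shows that the trial's main comparison is sound. It does not cure section 6.1.2, which gives a post-switch reading the same primary label. A testing hierarchy would settle the error rate but not the bias.

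Some stronger readings are tempting and are not supported:

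- **That the protocol itself claims lasting benefit.** Section 1.2 says HBOT "has been shown in several clinical studies to have the capacity to induce neuroplasticity in injured brains even years after an acute insult". This concerns how long after an injury HBOT can still act, not how long its benefit lasts once it stops. The structural mechanisms listed there make carry-over plausible and no more.
- **That the crossed-period difference will be about zero.** That is the 100% persistence end of an assumed range from 0 to 30 points.
- **That the trial's type I error is 9.75%.** No rule says that either reading suffices, and the readings come from the same patients, so independence is unlikely.
- **That the order of treatment is not randomised.** The offered sequence follows from the 1:1 allocation. Acceptance of the switch is what is not randomised.

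The dilution and the false-positive figure also belong to different situations. The first assumes HBOT is better, and the second assumes no difference.

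**Conclusion.** The point holds as a fault in what section 6.1.2 fixes. Two readings carry primary status, neither is named as decisive, and the later one cannot give an unbiased HBOT-versus-medication effect, because switching is optional, no washout is stated and only completers are analysed. That conclusion follows from the text alone.

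The sizes are conditional. The possible distortion runs from none to the whole planned 30-point difference, depending on an assumed persistence share and on full switching. The type I error is at most 9.75% and applies only if either reading may support the primary conclusion. The randomised 3-month comparison and its sample size are not affected.

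**What to change.** In section 6.1.2, state that the sole confirmatory primary analysis is the randomised between-arm comparison at the 2nd (3-month) evaluation, before any switch, and define the primary analysis set by reference to period 1. Label crossed-period data as secondary or descriptive, and report them by sequence together with the number in each arm who accepted the switch.

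This changes wording only. No treatment or visit changes, alpha stays at 5% two-sided, and the sample size stays at 58 evaluable and 70 in total. The cost is that the sponsor gives up a primary-level claim from the crossed period.

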### 3.2.2 Pharmaceutical protocol

Patients will be offered pharmacological treatment with one of the two medications currently licensed for the treatment of FMS in Israel, i.e. Cymbalta and Lyrica. Treatment with Lyrica will start at a dose of 75 mg at bedtime while treatment with Cymbalta will start at a dose of 30 mg a day (in the morning). After a period of 6 weeks patients will be evaluated and dose will be adjusted as necessary. Patients may also be switched from one medication to the other based according to clinical judgment.

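### The primary efficacy set keeps only completers without major violations, so the superiority comparison can be biased, in a direction and by an amount the protocol does not let one determine

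*Protocol*

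**What the plan says.** Section 6.1.2 of the protocol fixes the primary set: "The primary efficacy analysis evaluation will include all subjects who completed the treatment period, had no major protocol violations". The only other set is in section 6.1.1: "The safety analysis set will consist of all subjects with whom the study treatment was initiated". The protocol contains no efficacy set made up of everyone randomised.

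The arms differ in kind. Section 3.2.1 gives one arm 60 chamber sessions, five per week. For the other, section 3.2.2 states: "Patients will be offered pharmacological treatment with one of the two medications currently licensed". It allows a change from one drug to the other on clinical judgment. Section 3.2 adds education and advice on non-drug measures. No sham treatment or blinding of patients is described.

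The primary endpoint in section 4.1 is daily pain on a 0 to 10 visual analogue scale (VAS). Section 6.1.2 refers instead to fibromyalgia questionnaire scores. Either way the patient rates the outcome. Section 3.2.3 places the second evaluation at 3 months, before patients may switch arms.

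Section 6.1.2.1 sizes the trial on "a reduction of 50% in the HBOT group and a reduction of 20% in the medication group", "with a standard deviation of 40" (percent). It then gives: "Assuming a power of 80%, and 5% two-sided level of significance", "a total of 58 participants would be required, 29 participants in each arm". It adds: "Considering a dropout rate of 15% the total sample size required is 70".

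**The concern.** Section 2 asks a superiority question. It says a decisive advantage over standard of care is needed to justify the time and resources that the chamber course takes. That calls for the effect in everyone assigned to each strategy, including those who do not finish.

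Randomisation balances the arms at entry. It does not balance the subgroups that remain after patients have been removed for what happened later. Finishing 60 sessions and staying on an offered, switchable drug are different hurdles, so the patients who leave each arm may differ in number and in how they were faring. Because patients and staff know the assignment and pain is self-rated, the decision to stop can be tied to the outcome. If that tie differs by arm, the completer difference mixes treatment effect with selection, and the nominal 5% error rate no longer holds.

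**Working it through.** **Inputs from section 6.1.2.1:** reductions of 50% and 20%, so a difference of 30 points; SD 40; two-sided 5%; 80% power; 15% dropout; 70 patients, or 35 per arm at 1:1 (section 5.4).

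**1. The plan's own figures.** The standardised effect is 30/40 = 0.75. A two-sample t-test needs 28.9, so 29 per arm and 58 in total, with power 80.1%. For dropout, 29/0.85 = 34.1, so 35 per arm and 70 in total. Both stated figures reproduce.

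**2. Power of the completer analysis.** At the planned loss, 70 × 0.85 = 59.5 remain and power is 81.2%. With 12 of 70 lost (17.1%), 58 remain and power is 80.1%. It falls below 80% from the 13th loss. Since 59.5 − 58 = 1.5, the dropout allowance leaves room for one or two further exclusions for violations.

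**3. Selection bias under no true effect.** *Assumption:* both arms have the same true mean, SD is 40, and a fraction q = 0.15 is lost through a tendency to leave that has correlation ρ with poor outcome. The mean of those who stay shifts by

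SD × ρ × φ(z_q)/(1 − q), with z_0.15 = −1.036 and φ = 0.233.

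- ρ = 1 (exactly the worst 15% leave): 40 × 0.233/0.85 = 11.0 points.
- ρ = 0.5: half of that, 5.5 points.

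Simulated trials with 35 per arm and 5 of 35 lost in each (14.3%) give slightly smaller shifts:

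| Outcome-related loss | Mean bias | Type I error |
|---|---|---|
| HBOT arm only, ρ = 0.5 | about 5 points toward HBOT | about 8% |
| Drug arm only, ρ = 0.5 | about 5 points toward drug | about 8% |
| One arm only, worst leave | about 10 points toward that arm | about 20% |
| Both arms, equal strength | none | – |

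Against the planned 30 points, 5 is one sixth and 11 is a little over one third.

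**4. Power if all 70 are analysed (35 per arm).**

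- The 30-point difference and SD 40 hold in everyone: 87.1%.
- Difference detectable with 80% power at SD 40: 0.68 × 40 = about 27 points.
- *Assumption:* the 15% who stop in each arm have no mean reduction. The difference is 0.85 × 30 = 25.5. With SD kept at 40, power is 75%. Mixing stoppers and completers widens the spread: variance is 1600 + 0.15 × 0.85 × 50² = 1918.75 in the HBOT arm and 1600 + 0.15 × 0.85 × 20² = 1651 in the drug arm. The pooled SD is √1784.9 = 42.2 and power is 70%.
- *Assumption:* HBOT stoppers improve only as much as the drug arm. The difference is again 25.5, the SD is 40.7 and power is 73%.
- *Harsher assumption:* only HBOT stoppers have no reduction. The difference is 0.85 × 50 − 20 = 22.5, and power is 64% at SD 40.

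**The case against.** Four points can be made for the plan.

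**The sample size already suits this analysis.** This stands. A reader might infer that restricting the set to completers undermines the stated 80% power. The documents do not support that: 58 and 70 reproduce, and the planned 15% loss leaves about 81%. The protocol gives no rate of major violations, and violators may overlap with dropouts. What remains is that the 15% is labelled as dropout only, with little slack beyond it.

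**The direction of bias is not given.** This also stands. A reader might infer that the more demanding chamber course must look better than it is. Drug intolerance or non-response can remove poor responders from the comparator just as well, and the sign then reverses. If outcome-related loss is equal in the two arms, mean bias is nil. The protocol gives no stopping reasons or rates, so the figures above are illustrations.

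**The statistical analysis plan may hold more.** It may add a supportive all-randomised analysis, rules for missing data and a definition of major violation. Their absence from the protocol is no finding. Nor does the protocol say that patients who stop will go unmeasured. But the choice of primary set is made in the protocol itself, and a supportive analysis elsewhere would not change which result is primary.

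**An all-randomised analysis can cost power.** This is true, and the amount depends on how those who stop fare. It is a reason to recheck the sample size alongside the change. It does not justify a primary comparison that randomisation no longer protects.

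**Conclusion.** The point holds for the analysis set. Section 6.1.2 conditions the primary superiority comparison on two events after randomisation, in a trial with unlike treatment courses, no described blinding and a self-rated outcome. Bias and an inflated type I error are possible; their direction and size are not known from the protocol.

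Under no true effect and about 15% loss per arm, outcome-related loss in one arm only (correlation 0.5) gives about 5 points toward that arm and type I error of about 8%. The 10 to 11 points and 20% when exactly the worst 15% leave one arm are an upper bound for that loss rate, not a forecast. That the design is unblinded is inferred from the absence of any sham or masking; the protocol does not use the term.

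This is not a sample-size error, and it does not show that the result will favour HBOT. It should be settled before the primary analysis because it determines the trial's main conclusion, and pain scores not collected from those who stop cannot be recovered later.

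**What to change.** In section 6.1.2:

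- Make all randomised patients, analysed in the arm assigned, the primary efficacy set for the first-period comparison.
- State that the 3-month VAS is collected from patients who stop treatment, at the second evaluation already planned in section 3.2.3.
- Keep completers without major violations as a supportive set.

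In section 6.1.2.1, restate power for the all-randomised set with its assumptions: 87% if 30 points and SD 40 hold in everyone; a detectable difference of about 27 points at 80% power; 70 to 75% if the 15% who stop in each arm have no reduction. Say also whether the 15% allowance covers only dropout.

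The cost is amendment wording and follow-up of stoppers at an existing visit. Stated power may fall by up to about 10 points if stoppers in both arms have no reduction, and by more if only HBOT stoppers do. Restoring 80% under the both-arms assumption would take about 80 patients (SD 40) to 90 (SD 42.2) in place of 70.
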